## Abstract

**Background:**

Anemia remains a public health challenge in Ethiopia, affecting an estimated 56% of children under age 5 years, 23% of women of reproductive age and 18% of adult men. However, anemia etiology and the relative contribution of underlying risk factors for anemia remains unclear and has hindered implementation of anemia control programs.

**Methods/design:**

Anemia Etiology in Ethiopia (AnemEE) is a population-based cross-sectional survey of six regions of Ethiopia that includes children, women of reproductive age, and men from regionally representative households. The survey will include detailed assessment of anemia, iron, inflammatory and nutritional biomarkers, diet, comorbidities, and other factors. The objectives of AnemEE are 1) to generate evidence for decision-making on the etiology of anemia in Ethiopia among men, women and children and 2) to simulate the potential effect of iron fortification and other interventions on the prevalence of anemia and risk of iron overload.

**Discussion:**

AnemEE will provide the most comprehensive evaluation of anemia etiology in Ethiopia to date due to its detailed assessment of diet, biomarkers, infections and other risk factors in a population-based sample. By generating evidence and simulating potential interventions, AnemEE will inform the development of high-impact anemia control programs and policies.

**Trial registration:**

ClinicalTrials.gov, NCT04002466. Registered on 28 June 2019. Retrospectively registered.

## Background

Worldwide, anemia affects over 1.5 billion people, which is approximately a quarter of the global population [1]. Anemia, or low hemoglobin concentration, is known to negatively affect cognitive and motor function, increase the risk of maternal and child death, and cause fatigue and low work productivity [2–4]. Due to the wide range of adverse effects of anemia, the World Health Assembly (WHA) established a commitment to halve anemia prevalence from 2011 levels in women of reproductive age by 2025 [1]. The national prevalence of anemia in the 2016 Ethiopia Demographic and Health Survey (DHS) was estimated to be 56% among children under the age of 5 years, 23% among women of reproductive age (15–49) and 18% among adult men (15–49), with greater prevalence in rural areas and regions with large pastoralist communities [5]. Ethiopia is strongly committed to promoting health and wellbeing in the country, and anemia control is a priority. However, the relative contribution of the underlying causes of anemia in Ethiopia remains unclear.

The causes of anemia in low- and middle-income countries are multifactorial. It is estimated that half of anemia cases worldwide are attributable to iron deficiency; however, these reports have not assessed the relative contribution of iron deficiency and other risk factors at regional or country levels [6]. Non-iron deficiency causes of anemia include parasitic diseases and infections such as malaria [7], hookworm infections [8], and schistosomiasis [9]; other micronutrient deficiencies including folic acid, vitamin A, and vitamin B12 [10]; and genetic hemoglobinopathies such as sickle cell disease and thalassemia [11].

The 2013 Ethiopian National Food Consumption Survey (ENFCS) found that dietary iron intake at the population-level in Ethiopia was high, particularly among adult men and women [12]. As determined by a single 24-h dietary recall, only 12.9% of women of reproductive age and 3.2% of adult urban men had inadequate iron intake. In contrast, there was a high prevalence of excessive iron intake; 64% of women of reproductive age and 89% of adult urban males had excessive intakes based on World Health Organization recommended tolerable upper intake levels [13]. However, the ENFCS was focused on diet and therefore did not include biomarkers of anemia and iron. The 2016 Ethiopian National Micronutrient Survey (ENMS) directly assessed iron biomarkers and determined that the prevalence of iron deficiency anemia (IDA) as assessed by ferritin was 17.8% among children and 5.8% among non-pregnant adult women [14]. However, the ENMS lacked dietary intake data and did not include adult men in the survey. In addition, seasonality is likely an important determinant of iron intake and anemia prevalence in Ethiopia; a recent small longitudinal study of 216 pregnant women in rural Oromia and Tigray regions found that the prevalence of anemia increased from 21.8% during postharvest season to 40.9% in pre-harvest season [15]. The ENMS and ENCFS were conducted in single rounds and therefore were not able to examine seasonal variation in iron intake and anemia prevalence.

In order to address the current evidence gaps, we are undertaking a population-based cross-sectional survey to evaluate anemia prevalence and etiology in Ethiopia. The Anemia Etiology in Ethiopia (AnemEE) study will assess anemia, dietary intake, iron and other nutritional biomarkers, soil-transmitted helminth infections, malaria, and inflammatory biomarkers among children, women of reproductive age, and men in six regions of Ethiopia. We intend to determine the magnitude and relative contributions of the underlying causes of anemia and simulate potential interventions, in order to guide high-impact and safe anemia control intervention programs and policies.

## Methods/design

AnemEE is a population-based cross-sectional survey of children, adult females of reproductive age and adult males in six regions of Ethiopia, carried out in two seasons. The AnemEE protocol was developed by collaborators at the Harvard T.H. Chan School of Public Health in the United States and Addis Continental Institute of Public Health in Ethiopia. The first participant was enrolled in the study on January 27, 2019 and data collection is expected to continue through August 2019.

### Primary objectives

The overall goal of AnemEE is to generate evidence on the etiology of anemia in adults and children in Ethiopia to inform anemia control efforts. The two primary aims of the study are to (a) determine the prevalence and relative contribution of risk factors for anemia, iron deficiency anemia, and potential iron overload among children aged 6–59 months, adult women of reproductive age (15–49 years) and adult men (15–49 years) in six regions of Ethiopia and (b) simulate the potential effect of iron fortification, improved sanitation, deworming and other interventions on anemia, IDA, and iron overload among children and adult men and women.

### Study population

AnemEE will be conducted in six regions of Ethiopia: Amhara, Tigray, Oromia, Addis Ababa, Afar and Southern Nations, Nationalities, and Peoples’ Region (SNNPR). These regions were selected due to differences in their agroecology, anemia prevalence, and potential for iron overload. In addition, these regions cover a range of agrarian, urban/rural and pastoralist communities. Children (aged 6–59 months) and adult women of reproductive age (15–49 years) are included in the study population due to known high risk of anemia and poor health outcomes. Adult men are included as iron overload is a concern if an iron fortification intervention were to be implemented. Due to differences in diet between seasons in Ethiopia, the survey will be repeated in 2 rounds; the first during the short Belg season (dry season February–April) and the second in the major Meher season (wet season May–September). Both survey rounds will be conducted in the same kebeles (the smallest administrative units in Ethiopia), but the second round will be conducted in a different quadrant of each kebele so that each survey includes different individuals.

A stratified two-stage sampling method will be used to obtain regionally representative samples of urban and rural children and adult women and men in each region in each of the two seasons **(**Fig. 1**)**. In the first stage, two zones from each region will be randomly selected, and within each zone, 3 woredas (districts that collectively make up a zone) will be selected **(**Fig. 2**).** Within each woreda, administrative data from the regional and district administrative offices will be used to randomly sample 2 kebeles (12 kebeles total per region). In the second stage of sampling, each kebele will be divided into quadrants and a central zone, and one of these five areas will be randomly selected. Within each selected area, random households will be visited until 30 eligible households are identified, which will each include at least one woman of reproductive age. Of these, a simple random sample of 17 households per kebele will be selected for participation in the study using computer generated random numbers. Of the 17 households in each kebele, 17 women aged 15–49 years (one per household), 10 children aged 6 to 59 months (no more than one per household) and 7 men aged 15–49 years (no more than one per household) will be included in the study.

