### Data collection

Field and specimen collection standard operating procedures were developed and piloted in one urban and one rural kebele. Training manuals including a comprehensive description of all field work and data collection procedures were used to train all study staff. Enumerators with experience in large-scale nutrition-related surveys were recruited and trained on the study procedures. Experienced phlebotomists were recruited and trained on specimen collection and processing in the field. A supervision plan was developed to maximize data quality.

In each survey, trained enumerators will visit participating households selected during the sampling process to enroll participants and obtain informed consent. For each participant, the enumerators will seek written informed consent for a blood draw to assess serum biomarkers of anemia and a stool specimen to screen for soil-transmitted helminth infections. After enrolling participants on the first visit, the enumerators will return on a separate occasion to administer the questionnaires and collect biological specimens from the woman selected from that household and also the man or child (if applicable for that household). If one of the study participants is not available at the time of interview, the enumerator will return to the household up to three times to complete the assessments and collect the biological specimens. If the participant is still not available after three visits, that participant will be excluded. Table 1 provides an overview of data that we plan to collect for each man, woman and child. All questionnaires and dietary assessments will be administered on tablets using an electronic data collection platform, SurveyCTO (developed by Dobility, Inc.). During the survey, data will be continuously uploaded and monitored for quality.

**Table 1 Tab1:** Questionnaire and biological assessments administered to women, children and men in the Anemia Etiology in Ethiopia (AnemEE) survey

Assessments	Women of reproductive age (15–49 years)	Children^a^ (6–59 months)	Adult Men (15–49 years)
Education, employment and other sociodemographic characteristics	X		X
Water, sanitation and hygiene	X		
Household characteristics	X		
Food fortification	X		
Pregnancy	X		
Morbidity in past 2 weeks	X	X	X
Household food sources	X		
24 h recall	X	X	X
Food frequency questionnaire	X	X	
Anthropometry (weight, height, MUAC)	X	X	X
Blood pressure	X		X
Hemoglobin	X	X	X
Malaria rapid diagnostic test	X	X	X

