## Discussion

Anemia remains a public health challenge in Ethiopia and prevention and evidence-based treatment strategies are urgently needed. However, there is a lack of information on anemia etiology, hindering the development of evidence-based anemia control efforts. To address the current evidence gaps, we designed the AnemEE survey to evaluate anemia etiology in Ethiopia. This cross-sectional survey in six regions of Ethiopia includes detailed assessment of usual dietary intake through the use of both a 24-h recall and FFQ, anemia and iron biomarkers, soil-transmitted helminth infections, malaria, and inflammatory biomarkers among a population representative sample of men, women, and children. These data are intended to determine the relative contributions of the underlying causes of anemia in order to guide high-impact and safe anemia control intervention programs and policies. To provide further guidance, we will also simulate the impact of introduction of iron fortification and other potential interventions on anemia and iron overload.

Although previous population-based studies in Ethiopia have assessed anemia, AnemEE is unique in that it assesses both anemia and risk factors simultaneously, enabling us to examine anemia etiology. AnemEE will also give us the ability to investigate the effect of seasonality on iron intake and anemia prevalence. Additionally, AnemEE has both consumption data and biological markers of anemia and iron status, which will allow us to estimate the effect of simulated dietary interventions on anemia and iron levels. The ENFCS simulations predicted that excessive iron intake would occur in adults and children in almost all regions if universal fortification of flours or oils were implemented, but this survey only had data on consumption and as a result could not model effects on anemia and excess iron [12]. Furthermore, we will also examine the effects of other health interventions such as deworming and improved sanitation, on reducing the prevalence of anemia and the risk of iron overload.

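### A simple random draw of 17 households screened only for a woman aged 15–49 does not assure the 10 children and 7 men per kebele, and it leaves men and children living without such a woman outside the survey

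*Protocol article*

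**What the plan says.** All references are to the protocol article.

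- **Study population, eligibility.** In the selected part of each kebele, households are visited at random until "30 eligible households are identified, which will each include at least one woman of reproductive age". No other household criterion is given.
- **Study population, draw.** From these 30, "a simple random sample of 17 households per kebele will be selected for participation in the study using computer generated random numbers".
- **Study population, yield.** The 17 households are to provide 17 women, one each, together with "10 children aged 6 to 59 months (no more than one per household) and 7 men aged 15–49 years", the men also limited to one per household.
- **Data collection.** Specimens and questionnaires are taken from "the woman selected from that household and also the man or child (if applicable for that household").
- **Blood and stool collection.** The 10 and the 7 are called targets.
- **Sample size.** 4896 participants over both rounds, raised to 5100 for precision.
- **Discussion.** The measurements are described as made "among a population representative sample of men, women, and children". Study population likewise claims regional representativeness for all three groups.

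**The concern.** Two separate problems follow from screening on women alone.

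**Yield.** A simple random sample of households that ignores whether a child or a man lives there fixes the number of women at 17. It leaves the numbers of children and men to chance. The text gives no rule for choosing which households supply a child or a man, and none for a shortfall, yet the sample size treats both counts as certain. Children have the least room, because their required number is close to the planned number.

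**Coverage.** A man aged 15–49 in a household with no woman aged 15–49 has zero chance of selection. So has a child aged 6–59 months in such a household. Study population says that men were included because of concern about iron overload under fortification, so a misdescribed male population bears directly on the iron-excess estimates and on the fortification simulation.

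**Working it through.** **1. Reproducing the planned total.** Inputs from Study population: "AnemEE will be conducted in six regions of Ethiopia"; "randomly sample 2 kebeles (12 kebeles total per region"); "the survey will be repeated in 2 rounds"; 17 + 10 + 7 = 34 persons per kebele and round.

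6 × 12 × 34 × 2 = 4896, exactly the stated figure. The total therefore assumes that every kebele delivers 10 children and 7 men in each round.

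**2. Required against planned, per region, both rounds pooled.** The inputs are 10-point precision, a design effect of 2.0, and 90% participation at household and at individual level (Sample size). Prevalences are the national figures in Background, used as an assumption because the regional ones are not printed.

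n = 1.96² × p(1 − p) / 0.10² × 2.0 / (0.9 × 0.9)

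| Group | p | Needed | Planned (24 kebele-rounds) |
|---|---|---|---|
| Children | 0.56 | 234 | 10 × 24 = 240 |
| Women | 0.23 | 168 | 17 × 24 = 408 |
| Men | 0.18 | 140 | 7 × 24 = 168 |

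Children have about 3% slack (240/234 = 1.03). The break-even is 233.7/24 ≈ 9.7 children per kebele.

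**3. What the simple random draw delivers.** Let K of the 30 listed households contain an eligible child. K is not in the documents, so a range is shown. The number of child households among the 17 drawn is hypergeometric(30, K, 17), and the yield is capped at 10. The half-width for children is 1.96 × √(0.56 × 0.44 × 2.0 / (n × 0.81)).

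| Share with a child (K) | P(at least 10) | Expected yield | Children per region (× 24) | Half-width, points |
|---|---|---|---|---|
| 40% (12) | 0.02 | 6.8 | 163 | 12.0 |
| 50% (15) | 0.23 | 8.4 | 202 | 10.8 |
| 60% (18) | 0.70 | 9.6 | 230 | 10.1 |
| 70% (21) | 0.98 | 10.0 | 239 | 9.9 |

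The shortfall is material at 40–50%, marginal at 60% and absent at 70%.

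**4. If a household gives a child or a man but not both.** This is an inference from Data collection and from 10 + 7 = 17. On that reading all 17 households must supply one or the other, so a single household with neither breaks the allocation. If 5% of households have neither (assumption), the chance that none of the 17 is of that kind is 0.95¹⁷ = 0.42; at 10% it is 0.90¹⁷ = 0.17. Now treat households as independent, and child and man presence as independent of each other. The chance of filling both counts is then 8% with child share 0.5 and man share 0.8, 55% with 0.7 and 0.9, and 99% with 0.8 and 1.0.

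**5. Coverage.** This needs no assumption about the child share. Eligibility requires a woman aged 15–49, so a household without one has selection probability 0. An inverse-probability weight is undefined for such a household. The size of the excluded group is not in the documents.

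**The case against.** **The counts may usually be met.** This is right where children are common: at a 70% share, 10 or more child households are drawn 98% of the time. A reader might infer that the design cannot deliver 10 and 7. The documents do not support that; it is a matter of probability, governed by a household composition they do not report.

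**The 10 and 7 are targets.** Blood and stool collection says so, and the words about applicability in Data collection foresee households that give only a woman. Both points stand, and the requirement of separate households in step 4 remains an inference. But the 4896 counts the targets as fully met, so the planned precision still depends on them.

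**The increase to 5100.** If spread proportionally (assumption), it raises the child target to 240 × 5100/4896 = 250 per region. Scaling the expected yields in the same way gives about 170, 210 and 240 children at 40%, 50% and 60%, against 234 needed. It removes the marginal shortfall at 60% but not those at 40% and 50%.

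**The allocation rule may be elsewhere.** The full protocol, the field procedures or Fig. 1, which was not available for this review, may contain it. For that reason one should not infer that undisclosed quotas were used or that women's prevalence is biased. No quota is described, a random sub-selection with weights need not bias anything, and Statistical analysis commits to accounting for the sampling design.

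**Timing.** Enrollment began in January 2019 and was still open in August 2019, so a changed draw could help only kebeles not yet fielded. Weighting and the wording of the target populations are unaffected by this.

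None of these objections meets the coverage point, which follows from the stated eligibility criterion.

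**Conclusion.** The concern holds in two parts.

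First, the stated draw does not assure the child and man counts on which the sample size rests. For children, the expected loss of precision runs from none at a 70% child share to about 2 points at 40% (12.0 against 9.9 for the full 240). This assumes the national prevalence of 56%, the plan's own design effect and participation rates, and rounds pooled within region, before the increase to 5100.

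Second, and independent of those assumptions, the male and child samples represent only men and children who live with a woman aged 15–49. The claims of representativeness are too wide as written, and design-based analysis cannot repair them. How far the estimates would move cannot be judged from the documents.

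**What to change.** 1. Restate the target populations as men aged 15–49 and children aged 6–59 months living with at least one woman aged 15–49. Qualify the representativeness statements in Study population and Discussion, and the conclusions on men's iron excess, to match.
2. At the 30-household listing, record whether a child and a man are present and how many persons in each group are eligible. Draw households and allocate the child or man interview at random using that composition. Every listed household, including those with both a child and a man and those with neither, must keep a known non-zero probability for each group in which it has an eligible member. In particular, the men should not be drawn only from households without a child, since that would exclude men living with young children.
3. Weight by the inverse of the selection probability, including the number eligible within the household. For rounds already fielded, build these weights where the forms recorded enough to allow it.
4. If the simple random draw is kept, restate the expected numbers of children and men and the precision that follows.

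The cost is a small change to the field form, a weighting step and some loss of efficiency from unequal weights. Item 1 costs only wording.

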**Fig. 1 Fig1:**
[figure not shown]
Sampling approach for the Anemia Etiology in Ethiopia (AnemEE) survey

**Fig. 2 Fig2:**
[figure not shown]
Zones and woredas included in the Anemia Etiology in Ethiopia (AnemEE) survey (Source: created by authors)

### Sample size

We calculated the minimum sample sizes required for each population group by region assuming the anemia prevalence determined in the 2016 Ethiopia DHS [5] by age, sex and region, 10% precision overall, 90% participation at the household, 90% participation at the individual level, and a design effect of 2.0. Between the two independent population level surveys, in the short Belg season (February–April) and in the major Meher season (May–September), a sample size of 4896 participants was calculated to provide regionally representative anemia estimates for children, adult women, and adult men in the six selected regions. We increased the total sample size to 5100 to increase precision.

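### The sampling scheme yields exactly 4896 participants, the stated total is 5100, and the visible text does not say where the other 204 are sampled

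*Protocol article*

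**What the plan says.** The Study population section gives a complete scheme. On regions: "AnemEE will be conducted in six regions of Ethiopia". On the upper stages: "two zones from each region will be randomly selected, and within each zone, 3 woredas". On kebeles within each woreda, the plan is to "randomly sample 2 kebeles (12 kebeles total per region"). Within a kebele, "a simple random sample of 17 households per kebele will be selected for participation", and these households supply "17 women aged 15–49 years (one per household") together with "10 children aged 6 to 59 months (no more than one per household) and 7 men aged 15–49 years". The same section says that both rounds use the same kebeles, with a different area of each kebele in the second round so that the individuals differ.

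The Blood and stool collection section gives the same per-kebele targets of 17 women, 10 children and 7 men.

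The Sample size section gives 4896 as the calculated number over the two seasonal surveys, and continues: "We increased the total sample size to 5100 to increase precision".

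**The concern.** Two sections of the current text lead to different totals. A reader who follows the sampling description selects 4896 people; a reader who cites the Sample size section reports 5100. The scheme reproduces the first figure exactly, so the sampling description appears to stand as it was before the increase.

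Two things depend on the answer. The first is the planned number against which achieved recruitment is judged. The second is weighting. The Statistical analysis section says that prevalence estimates will account for the sampling design, and the place where 204 more people are drawn determines selection probabilities and the balance across regions and seasons. For example, if kebeles are drawn with equal probability within a woreda, drawing 3 instead of 2 raises each kebele's selection probability by 3/2. Weights built on 2 would then be too large by a factor of 1.5 in that woreda.

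**Working it through.** **Inputs, all from the Study population section.** Regions: 6. Zones per region: 2. Woredas per zone: 3. Kebeles per woreda: 2. Women, children and men per kebele: 17, 10, 7. Rounds: 2, in the same kebeles.

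**Reproducing 4896.**
- Kebeles per region: 2 x 3 x 2 = 12, as stated. All regions: 6 x 12 = 72.
- People per kebele per round: 17 + 10 + 7 = 34.
- Per round: 72 x 34 = 2448. Both rounds: 2 x 2448 = 4896.
- By group over both rounds: 144 x 17 = 2448 women, 144 x 10 = 1440 children, 144 x 7 = 1008 men.

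This equals the calculated figure in the Sample size section.

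**Gap to 5100.** 5100 - 4896 = 204, which is 4.2% of 4896 and 4.0% of 5100.

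**Possible routes to 5100.**

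| Route | Arithmetic | Conflict with the text |
|---|---|---|
| More kebeles, each visited in both rounds | 5100 / (34 x 2) = 75 kebeles, or 12.5 per region | 12 kebeles per region |
| One extra kebele per region in one round only | 6 x 13 x 34 + 6 x 12 x 34 = 2652 + 2448 = 5100 | The same kebeles in both rounds, and 12 per region in that round |
| Larger uniform take in the same 72 kebeles | 5100 / 144 = 35.4 per kebele-round; 35 gives 5040, 36 gives 5184 | The 17, 10 and 7 targets; not a whole number |
| Unequal take across the 72 kebeles | 204 spread over 144 kebele-rounds | The 17, 10 and 7 targets |

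Non-participation cannot supply the difference, because it only lowers the number obtained. Nor is 5100 the result of inflating 4896 for the stated participation: 4896 / (0.9 x 0.9) = 6044.

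**A further check.** The Dietary assessment section has everyone in one kebele per region in each survey complete a second 24-hour recall, with a target of 400. At 34 per kebele this is 6 x 34 x 2 = 408. At 36 per kebele it would be 432. The target fits the scheme with 34 better.

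**Effect on precision.** If the increase is spread evenly and the design effect is unchanged, half-widths are multiplied by sqrt(4896 / 5100) = 0.980.

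For children per region with both rounds pooled, the number rises from 240 to 240 x 5100 / 4896 = 250. Half-width = 1.96 x sqrt(2.0 x p(1 - p) / (n x participation)). The design effect of 2.0 and the participation of 0.9 x 0.9 = 0.81 come from the Sample size section, and p = 0.56 is the national figure in the Background. Regional prevalences are not given, so p is an assumption, as is z = 1.96.
- p = 0.56, 81% participation: 1.96 x sqrt(0.4928 / 194.4) = 9.9 points, falling to 1.96 x sqrt(0.4928 / 202.5) = 9.7 points.
- p = 0.50, 81% participation: 1.96 x sqrt(0.5 / 194.4) = 9.9, falling to 9.7.
- p = 0.70, 81% participation: 1.96 x sqrt(0.42 / 194.4) = 9.1, falling to 8.9.
- p = 0.56, full participation: 1.96 x sqrt(0.4928 / 240) = 8.9, falling to 8.7.

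The gain is about 0.2 points throughout.

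**The case against.** The strongest reply is that the Sample size section separates two numbers, a calculated size and a later increase, and never presents 5100 as the product of the sampling scheme. On that reading the article describes a base design and omits the mechanism of a 4% top-up. That mechanism could sit in Fig. 1 (the sampling approach), in Fig. 2 (the zones and woredas) or in a fuller protocol. The change is also upward, so the calculated minimum is met either way.

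Part of this stands. The visible text cannot exclude that the top-up was properly specified elsewhere, and the consequence is modest. It does not remove the conflict, because the Study population section leaves no count open: each route in the table departs from something that it states. A figure that gave different counts would still have to be reconciled with that text.

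A reader might go further and infer that any added kebeles must fall in only some regions and so break the equal regional allocation. The documents do not support this. Since 204 = 6 x 34, one extra kebele per region in a single round reaches 5100 with regions still equal; it unbalances the seasons instead. Nor do they establish that 75 kebeles were sampled. That is one arithmetic possibility, and the article never states it.

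**Conclusion.** The point holds as an internal inconsistency: the scheme in the Study population section gives 4896, the Sample size section gives 5100, and the visible text does not locate the 204 participants between them. The count is exact and needs no assumption beyond the stated design. The precision figures rest on an even spread, an unchanged design effect and an assumed prevalence.

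The size is small: 4.2% in number and about 2% in half-width. It does not invalidate the design. It would also be wrong to read the article as promising a substantial gain, since it says only that precision increases, and a factor of 0.98 is an increase. What matters is that the planned total is ambiguous and that the weights depend on how it is resolved.

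**What to change.** Reconcile the Study population and Sample size sections according to what was actually done.
- If the scheme was not enlarged, restate the total as 4896 and delete the sentence on the increase.
- If it was enlarged, correct the number of kebeles or the per-kebele targets to those that give 5100, by region and by round. Amend the statements on 12 kebeles per region or on the same kebeles in both rounds where they no longer hold, and carry the resulting selection probabilities into the survey weights.

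The Study status section reports recruitment still under way in August 2019, so the study team should know which case applies. Reverting to 4896 without checking could misreport a study that was in fact enlarged. The cost is a sentence or two of text and, in the second case, a check of the weights. No new data are needed.
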